It can be concluded that psychosexual support after treatment for GC should include motivational issues and psychosexual interventions to increase dilator compliance and improve sexual functioning. Furthermore, involvement of the partner is preferred. There is a need for a condensed, practical and (cost-)effective sexual rehabilitation intervention, consisting of psycho-education combined with elements of psychosexual-based cognitive behavioural therapy for GC patients and their partners after RT [27–31]. Therefore, based on the results of our previous studies [17, 18, 21], we developed a nurse-led sexual rehabilitation intervention to support sexual improvement and vaginal dilator use after RT. The intervention has multiple aims: motivating women, giving tailored advice, strengthening self-management, promoting couples’ mutual coping and support processes and, for women who received EBRT+BT, providing information and coaching on use of vaginal dilators on a regular basis. The results of our pilot study regarding the feasibility of the intervention demonstrated that this intervention improved women’s sexual functioning and that it supported them in their dilator use [32]. Furthermore, the nurses who were trained and supervised to guide the intervention felt capable to support the women.

In this manuscript we present the design of the SPARC (Sexual rehabilitation Programme After Radiotherapy for gynaecological Cancer) study, a multicentre randomized controlled trial (RCT) which evaluates the (cost-)effectiveness of the nurse-led sexual rehabilitation intervention in improving sexual functioning and dilator use of GC patients after RT. Participants are randomized to either the intervention- or optimal care as usual (CAU) control group (1:1). We expect that women who receive the intervention will report a statistically significant greater improvement in sexual functioning and – for women who receive EBRT+BT – higher compliance with dilator use, from baseline to 12 months post-RT than women who receive CAU.

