#### Outcome measures

Detailed descriptions of the outcome measures are provided in Table 2. The primary outcome measure is a standardized patient-reported outcome measure (PROM) assessing sexual functioning (Female Sexual Function Index (FSFI) [36]). The secondary outcome measures include PROMs assessing vaginal symptoms and body image concerns (European Organization for Research and Treatment of Cancer Quality of Life Questionnaire-Gynaecological Cancer Module (EORTC QLQ-CX24) [37]), fear of coital and non-coital sexual activity (Fear of Sexuality Questionnaire (FSQ) [38]), sexual distress (Female Sexual Distress Scale (FSDS) [39]), treatment-related distress (Impact of Event Scale (IES) [40]), generic health-related quality of life (European Organization for Research and Treatment of Cancer Quality of Life Questionnaire Core 30 (EORTC QLQ-C30) [41]), urological and gastrointestinal symptoms and sexual interest (European Organization for Research and Treatment of Cancer Quality of Life Questionnaire-Endometrial Cancer Module (EORTC QLQ-EN24) [42]), psychological distress (Hospital Anxiety and Depression Scale (HADS) [43]), and relationship satisfaction (Maudsley Marital Questionnaire (MMQ) [44]). To minimize respondent burden, the T1-questionnaire includes only the FSFI [36] and the FSDS [39].

**Table 2 Tab2:** Study outcome measures and corresponding questionnaires

Variable	Questionnaire	Details

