**Primary Outcome**		
Sexual functioning	FSFI [36, 45]	• Assesses overall sexual functioning • 19 items; 5- and 6-point Likert scales • Subscales: sexual desire; arousal; lubrication; orgasm; satisfaction; pain • Total score*: 2-36/Subscale scores*: desire 1.2-6; arousal 0-6; lubrication 0-6; orgasm 0-6; satisfaction 0-6. Higher score indicates better overall sexual functioning. A subscale score of 0 indicates no sexual activity • Time frame: past 4 weeks • Cronbach’s alpha in a gynaecologic cancer survivors group: total score: α = 0.94; subscale scores: 0.85 ≤ α ≤ 0.94 [46] • We added 4 items (6- and 7-point Likert scales) to assess the average frequency and amount of pleasure experienced during sexual activity without sexual intercourse and sexual activity with sexual intercourse • As our study sample consists of partnered as well as unpartnered women, we added an answer option ‘not applicable, no partner’ to the two items concerning the partner relationship

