### Statistical methods

#### Power and sample size calculation

The FSFI [36] is the primary outcome measure on which sample size calculations are based. With a total sample of 128 women (64 per group), and under the assumption of no interaction, the study will have a 80% power to detect a 0.5 standard deviation difference (Cohen’s effect size [57]) for the main effects of the sexual rehabilitation intervention, with the p-value set at 0.05 (two-sided test). Based on our pilot study we expect an attrition rate of 40% (i.e., women who discontinue participation in the study due to somatic reasons such as cancer recurrence) [32]. Consequently, we have to include at least 107 women in both study groups ultimately resulting in an intended sample size of 220 women [57].

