### Statistical analysis

T-tests or appropriate non-parametric statistics for independent samples will be used to evaluate the comparability of the intervention and control group at baseline in terms of sociodemographic and clinical characteristics. If, despite the stratified randomization procedure, the groups are not comparable on one or more background variables, those variables will be employed routinely as covariates in subsequent analyses.

Questionnaire scores will be calculated according to published scoring algorithms. Differences in changes in the primary outcome measure and secondary outcome measures between groups (intervention vs. control group) over time (T1-T5) will be evaluated using multilevel models and are based on an intention-to-treat approach. Effect sizes will be calculated using standard statistical procedures.

Furthermore, multilevel models will be used to investigate if improvement in sexual functioning in the intervention group is moderated by treatment/cancer characteristics and patient characteristics or mediated by e.g. sexual symptoms and vaginal symptoms or frequency of dilator use. Cost-effectiveness will be analysed using net benefit analysis, with multiple imputation to account for missing data.

Per protocol analyses will also be carried out (as a secondary analysis), comparing women who meet minimal compliance levels with the intervention with the control group. We will use correlation analyses to examine the relationship between degree of intervention adherence and intervention effect.

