The SPARC study has several notable strengths, including the randomized trial design, the multicentre nature (with participation of all Dutch GC centres), the comparison of the intervention group with a control group, the use of a clear treatment protocol and training protocol, the use of intention-to-treat analyses and the long-term follow-up assessments of outcomes. This trial also has several limitations. First, even though the FSFI is one of the most widely used questionnaires to measure sexual functioning among female cancer survivors, it produces biased results for women who have not been sexually active in the past month [36, 58]. The majority of the questions (15 out of 19) include a response option of ‘No sexual activity’ or ‘Did not attempt intercourse’, scored as zero. This is problematic because lower scores indicate more severe dysfunction whereas not engaging in sexual activity during four weeks does not necessarily imply sexual dysfunction. Sexual inactivity could have multiple reasons, such as the absence of a partner. As our study sample consists of partnered as well as unpartnered women, we chose to randomize participants stratified by having a partner. Second, despite the proposed benefits of regular dilator use (i.e., preventing or minimising vaginal stenosis), unequivocal evidence for its effectiveness in reducing vaginal complaints and better sexual functioning is still limited. The consequences of stenosis remain individually determined, with some women unaffected by significant vaginal complaints, while others experience long-lasting sexual problems [11]. However, because dilator use aims to prevent or minimise stenosis, we expect that this could positively affect vaginal complaints and sexual functioning indirectly. Therefore, we will include dilator use as a mediator instead of an outcome measure in the statistical analyses. Third, because RT-induced sexual problems develop soon after treatment, we start evaluating GC survivors early in the recovery phase and continue until 12 months post-RT. A longitudinal study that analysed functioning and symptom scores for quality of life of cervical cancer patients who underwent EBRT+BT demonstrated that RT-induced sexual problems increased to a clinically relevant degree in the first three months, after which it stayed elevated, even after 12 months [59]. This study did not include a sexual rehabilitation intervention. By offering a nurse-led sexual rehabilitation intervention we hope to find significant greater improvement in sexual functioning between the intervention- and optimal CAU control group at 12 months follow-up. However, it is possible that sexual functioning among GC survivors might improve further after 12 months post-RT. Therefore, we intend to plan an additional long-term follow-up measure at 24 months post-RT. Fourth, the possibility of contamination of our optimal CAU control group exists. In the past few years, the Dutch CAU regarding sexual problems after RT improved and was aligned nationwide, possibly as a consequence of the findings of our pilot study [32]. This resulted in fewer differences between the participating centres in the current trial, as all participating women are offered an information session, information booklet and a dilator set (if applicable) post-RT free of charge. In the current study, this improved CAU, combined with the possibility that the specialized trained nurses also come into contact with the control group, may result in the control group receiving better post-RT psychosexual care than intended - as the nurses might find it difficult not to use the additional trained skills to help these patients. This well-known problem of contamination within individually randomized intervention studies could be avoided by cluster randomization (i.e., on centre level instead of patient level). However, this method also introduces other potential threats to internal validity, as the number of centres in our study is limited and only a part of the centres could be randomized (n = 8, as a consequence of the training that was already completed in two centres for the pilot study) [32]. Because of the specific variation in the patient population, RT treatment procedures and follow-up procedures across centres, we decided to randomize on patient level, with the risk of contamination. During their training, the nurses received clear instructions on the procedure to be followed in both study groups and about the contamination risks.

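### The expected effect is a difference at 12 months, but the analysis covers change over T1-T5 with no deciding contrast, and the sample size is for a main effect

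*Protocol article*

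**What the plan says.** Four places in the protocol article bear on the primary claim.

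- **Hypothesis.** The Discussion (third limitation) fixes the time point: "we hope to find significant greater improvement in sexual functioning between the intervention- and optimal CAU control group at 12 months follow-up". The Abstract, the Background and the opening of the Discussion word it as greater improvement over an interval; in the Background it runs "from baseline to 12 months post-RT than women who receive CAU".
- **Analysis.** The Statistical analysis section evaluates "Differences in changes in the primary outcome measure and secondary outcome measures between groups (intervention vs. control group) over time (T1-T5") by multilevel models under intention to treat. It names no time point or contrast as decisive.
- **Sample size.** Power is calculated "for the main effects of the sexual rehabilitation intervention", and "under the assumption of no interaction". The article does not say which interaction is meant.
- **Outcome.** The Outcome measures section names the instrument: "The primary outcome measure is a standardized patient-reported outcome measure (PROM) assessing sexual functioning (Female Sexual Function Index (FSFI"). Table 2 describes it with the line "Assesses overall sexual functioning" and gives a total score and six subscales. The total score is tied to 12 months only in the definition of an improved patient for the cost-effectiveness analysis.

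**The concern.** A difference at 12 months, a difference in trajectory over five assessments, and a main effect are three different estimands. They can give different answers in the same data. A benefit that appears at month 3 and is gone by month 12 is a genuine group-by-time effect, but it is not the stated hypothesis. Conversely, a main effect with no group-by-time interaction would not be what a test of differences in change over time is built to isolate.

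The Discussion foresees nationwide implementation directly after completion if the intervention is proven effective. The p-value behind that statement should be a test of the effect the trial says it expects, at the stated 5%.

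**Working it through.** **Inputs from the article.** 64 evaluable women per arm, 0.5 SD, two-sided 0.05, 80% power, 40% attrition (Power and sample size calculation); assessments at baseline and at 1, 3, 6 and 12 months (Data collection).

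**Assumptions, because the article gives no figure.** Unit SD at every wave, compound symmetry with within-woman correlation ρ = 0.3, 0.5 or 0.7, complete data, and the effect profiles named below.

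**1. The plan's own figure.** For one comparison of two means, n = 2(1.96 + 0.842)²/0.5² = 62.8, so 63 per arm by the normal approximation; the t-test gives 63.8, so 64. Power at 64 per arm is 0.80 (t-test). Attrition: 64/0.6 = 106.7, so 107 per arm, 214 in total, rounded up to 220. The stated figures reproduce. They are those of a single 1-df comparison.

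**2. Between-arm differences in change from T1.** With n per arm, each of the four differences (T2 to T5) has variance (2/n)·2(1−ρ), and each pair has covariance (2/n)(1−ρ). So V = (2/n)(1−ρ)(I + J), where J is the 4×4 matrix of ones, and V⁻¹ = [n/(2(1−ρ))](I − J/5).

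**3. Effect of 0.5 SD at T3 only, zero at T5.** The joint 4-df test has noncentrality

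λ = [64/(2(1−ρ))] × 0.25 × (1 − 1/5) = 6.4/(1−ρ),

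which is 9.1, 12.8 and 21.3. The 5% critical value of chi-square on 4 df is 9.49.

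| Test | ρ = 0.3 | ρ = 0.5 | ρ = 0.7 |
|---|---|---|---|
| Joint group-by-time, 4 df | 67% | 83% | 97% |
| Average over T2-T5 | 12% | 15% | 21% |
| T5 contrast, 1 df | 5% | 5% | 5% |

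The T5 row is 5% by construction, since the effect at T5 is zero.

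**4. Other profiles with zero effect at T5.** With 0.5 SD at both T3 and T4, the joint test is significant with probability 86%, 96% and 99.8%. With a smoother profile of 0.25, 0.5, 0.25 and 0 SD at T2 to T5, it is 61%, 77% and 95%.

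**5. If a significant result at any wave counted as success.** Four independent tests would give 1 − 0.95⁴ = 18.5%. With correlation 0.5 between the four test statistics, simulation gives about 15%; over correlations 0.3 to 0.7 the range is 13% to 17%.

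**6. Power of a single T5 contrast for a true 0.5 SD at T5.** As a raw change, the standard error is √[(2/64)·2(1−ρ)] = √(1−ρ)/4, that is 0.209, 0.177 and 0.137. Power is 67%, 81% and 95%. Adjusted for baseline, it is 84%, 90% and 98%.

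**The case against.** The strongest reply is that no contradiction exists. T1-T5 is exactly baseline to 12 months, so the analysis sentence covers the interval named in the hypothesis. That holds for the Abstract, the Background and the opening of the Discussion, which are compatible with either reading. Only the third limitation in the Discussion is explicit about the time point, so it would be wrong to infer that the article states a 12-month test repeatedly.

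A second reply is that time coding, the deciding contrast and multiplicity belong in an analysis plan that is not shown. That is fair for model detail, and such a plan may settle the matter. It does not explain why the article itself gives three targets for one claim.

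Third, the article does not name a joint 4-df test, and an effect at month 3 only is extreme when sessions continue at 6 and 12 months. Both are true. The profile is an illustration, but the smoother one in the working leads to the same conclusion.

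Some stronger readings are tempting and should not be drawn:

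- *That every way of running the analysis misses the question.* Tests at each wave include T5. The inflated error arises only if a result at any wave counts as success, which no section says.
- *That a linear time slope would lose a true effect.* The article specifies no slope. A loss appears only if the full effect is already present at T2, the same month as the first session. If it starts at T3, the slope has power 78%, 90% and 99%, above the T5 contrast. The non-linear course cited in the Discussion comes from a study without such an intervention and is not a between-arm difference.
- *That six FSFI subscales are co-primary.* The entry "Subscales: sexual desire; arousal; lubrication; orgasm; satisfaction; pain" describes the instrument, as Table 2 does for other questionnaires. The total is the likely intended score, though the primary analysis does not say so.

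**Conclusion.** The point stands in this form: the deciding test is not named, and on its natural reading it does not match the effect the Discussion expects. Run as a joint group-by-time test, the analysis would be significant with probability about 67% to 97% for a 0.5 SD effect at month 3 only, with no effect at 12 months. The 12-month contrast would be significant 5% of the time. The exact percentages rest on 64 per arm, complete data, compound symmetry and the assumed correlations and profiles; the direction holds over the whole range shown.

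This shows that the trial could be called positive without a 12-month effect, not that it will be. The sample-size arithmetic is sound. Only the target it is written for needs aligning.

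**What to change.** State in the Statistical analysis section that the primary test is the single 1-df between-arm difference in change in FSFI total score from T1 to T5, estimated from the multilevel model with time as a categorical factor, at two-sided 0.05. Make the T2-T4 contrasts, the overall trajectory and the FSFI subscales secondary. In the power section, replace the main-effect and no-interaction wording with this same contrast.

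The cost is one or two sentences. Visits and data stay as they are, and so does the sample size, because 64 per arm is already the number for one 0.5 SD comparison. If the within-woman correlation may be as low as 0.3, adjusting for baseline rather than using a raw change keeps power above 80% (84% against 67%).

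The downside is that an effect seen only at an intermediate visit can no longer carry the primary claim. That is consistent with the effect the Discussion sets out to find.

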CAU = Care as usual; CEQ = Credibility/Expectancy Questionnaire; EORTC QLQ-C30 = European Organization for Research and Treatment of Cancer Quality of Life Questionnaire-Core 30; EORTC QLQ-CX24 = European Organization for Research and Treatment of Cancer Quality of Life Questionnaire-Gynaecological Cancer Module; EORTC QLQ-EN24 = European Organization for Research and Treatment of Cancer Quality of Life Questionnaire-Endometrial Cancer Module; EQ-5D-5 L = EuroQol 5D-5 L; FSDS = Female Sexual Distress Scale; FSFI = Female Sexual Function Index; FSQ = Fear of Sexuality Questionnaire; HADS = Hospital Anxiety and Depression Scale; IES = Impact of Event Scale; MMQ = Maudsley Marital Questionnaire; QoL = Quality of Life

Additionally, the secondary outcome measures include a 4-item questionnaire for women treated with EBRT+BT regarding the frequency of dilator use: (1) ‘How often have you used the dilator in the past month?’, (2) ‘Which size(s) dilator(s) did you use?’, (3) ‘How often did you have other kinds of penetration (including penile penetration) in the past month?’, and (4) ‘How often did you use petroleum jelly (Vaseline) tampons?’.

Furthermore, the following vaginal symptoms are assessed by standardized clinical examination for all participants: dryness, shortening/tightening, mucositis, discharge, blood loss, fibrosis, atrophy, pain, length (in millimetre) and dyspareunia. Vaginal symptoms will be recorded using the Common Terminology Criteria Sexual rehabilitation after RT for gynaecological cancers for Adverse Events (CTCAE), version 4.037.

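### As worded, moderators and mediators are sought for improvement within the intervention arm, which cannot separate effect modification from prognosis and cannot identify mediation

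*Protocol article*

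**What the plan says.** The Statistical analysis section first sets the main comparison: differences in change "between groups (intervention vs. control group) over time (T1-T5) will be evaluated using multilevel models", by intention to treat. The next paragraph turns to moderation and mediation and changes the target. Multilevel models will "investigate if improvement in sexual functioning in the intervention group is moderated by treatment/cancer characteristics and patient characteristics or mediated by" other variables, and the candidates are given as "mediated by e.g. sexual symptoms and vaginal symptoms or frequency of dilator use". No interaction of arm with a characteristic and no effect of arm on a mediator is stated there or elsewhere.

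The Discussion adds that "we will include dilator use as a mediator instead of an outcome measure in the statistical analyses", without saying which arms enter that model.

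The candidate mediators are not collected in one arm only. The text after Table 2 describes "a 4-item questionnaire for women treated with EBRT+BT regarding the frequency of dilator use" and says that "the following vaginal symptoms are assessed by standardized clinical examination for all participants". The Study groups section gives dilator sets and dilation advice to EBRT+BT women in both groups.

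The Power and sample size calculation section rests on a main effect: "With a total sample of 128 women (64 per group), and under the assumption of no interaction", the study has "80% power to detect a 0.5 standard deviation difference".

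**The concern.** A moderator is a characteristic across which the difference between arms varies. A mediator is something that the intervention changes and that in turn changes the outcome. Both definitions need the randomised contrast. Within the intervention arm alone, treatment does not vary, so neither quantity can be estimated.

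The risk is concrete in this trial. Type of radiotherapy is an obvious candidate among the treatment characteristics. The Background section says that EBRT+BT in particular harms sexual functioning. The Discussion cites a longitudinal study of EBRT+BT patients without a rehabilitation intervention whose sexual problems rose over the first three months and stayed raised. Type of radiotherapy may therefore predict FSFI change in either arm. A one-arm analysis could then label it a moderator even if the intervention helps all women equally.

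For dilator use, the first link in the mediation chain is whether the intervention raises use above that in the control arm. A one-arm analysis discards that link although the data exist. At stake are the trial's secondary statements about who benefits and by what route.

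**Working it through.** **1. The plan's own sample size.** Inputs from Power and sample size calculation: 0.5 SD, 80% power, two-sided 0.05, 40% attrition. A two-sample t-test needs 63.8, so 64 per group, with power 80.1%. Then 64 / 0.6 = 106.7, so 107 per group and 214 in total, which the plan takes up to 220. With 220 enrolled, 220 × 0.6 = 132 completers, or 66 per arm. The stated figures reproduce.

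**2. What a one-arm comparison estimates.** Take a two-level characteristic. Let p be its effect on change without the intervention, and m the amount by which it alters the intervention effect.
- Difference between levels in the intervention arm: p + m.
- Difference between levels in the control arm: p.
- Difference of the two, which is the interaction: (p + m) − p = m.

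The one-arm analysis estimates p + m and cannot split it.

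**3. How often a purely prognostic factor would pass as a moderator (m = 0).** Assumptions not in the document: characteristic split evenly (33 v 33 of the 66 completers), t-test at two-sided 0.05, p expressed in SD of change.

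| p (SD) | 33 v 33 | 46 v 20 |
|---|---|---|
| 0.3 | 22% | 20% |
| 0.5 | 52% | 45% |
| 0.7 | 80% | 73% |

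A simulation with 64 per arm, an even split and unit SD agrees. The one-arm test rejects in about 22%, 51% and 88% of trials at p = 0.3, 0.5 and 0.8, while the two-arm interaction test rejects in about 4% to 5%.

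**4. The opposite error.** With m = 0.5 and p = −0.5, p + m = 0. In the simulation the one-arm test finds this true modifier in about 5% of trials, the interaction test in about 29%.

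**5. Mediation.** Simulate a variable that the intervention does not affect but that predicts outcome with slope 0.5 (64 per arm, unit SDs). Its association with outcome within the intervention arm is significant in about 97% of trials. The effect of arm on the variable, which is truly zero, is significant in about 5%. Only the second check shows that the variable is not a mediator, and it needs the control arm.

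**6. Power of the valid interaction test.** With n per arm and share q at one level, SE = √(2/(nq) + 2/(n(1 − q))) in SD units. For n = 64:
- q = 0.5: SE = √(0.0625 + 0.0625) = 0.354. Power for m = 0.5 is Φ(0.5/0.354 − 1.96) = Φ(−0.55) = 29%. The difference detectable at 80% power is (1.96 + 0.84) × 0.354 = 0.99 SD.
- q = 0.3: SE = 0.386, power 25%, detectable difference 1.08 SD.

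**The case against.** The strongest reply is that the phrase is loose shorthand. Moderation and mediation usually refer to an intervention effect, the preceding paragraph sets up multilevel models on both groups, the Discussion brings in dilator use as a mediator without an arm restriction, and the mediators are collected in both arms. This is plausible. A reader might infer that a one-arm analysis is certainly intended, and the document does not establish that. But the only sentence that states the target of these analyses names one arm, and nothing corrects it.

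Four stronger readings are also tempting and do not hold.
- That the one-arm analysis finds only prognostic factors. It finds prognosis plus any modification, inseparably. Likewise, a mediator–outcome association within one arm is one component of mediation, though insufficient alone. A factor that predicts FSFI level but not change need not appear at all.
- That the dilator mediation is wrongly extended to women who had EBRT only. The questionnaire is for EBRT+BT women and the dilator hypothesis is confined to them throughout, so the restriction is already implied.
- That 52% or 80% is this trial's error rate. These figures depend on an assumed prognostic effect and split, and on a t-test in place of the planned multilevel model. Data collected before withdrawal are also kept, so 66 need not be the number analysed.
- That implementation would be steered to the wrong women. The document plans nationwide use if the intervention proves effective, not targeting by moderator.

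Finally, model details such as visit order and confounder adjustment belong in an analysis plan that is not shown, and their absence is no fault here. The population named for the analysis is different: the article fixes it, and fixes it badly.

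**Conclusion.** The point holds for the text as written. Moderators and mediators of improvement in the intervention group alone cannot be read as modifiers or mediators of the intervention effect. If a two-arm model is meant, the defect is one of wording; if not, the analysis cannot answer its question. The sponsor should settle which before analysis.

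The rates in the working show the size of the problem for a factor that is purely prognostic for change: about 22% to 80% false moderators over 0.3 to 0.7 SD with an even split, against about 5% with an interaction test. They rest on the assumptions listed there and illustrate the mechanism. These are secondary analyses, and the primary intention-to-treat comparison and the sample size are unaffected.

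**What to change.** Delete the phrase that limits the analysis to the intervention group, and state that:
- moderators are tested as arm-by-characteristic (by time) interactions in the full randomised sample;
- mediation is analysed in both arms with randomised arm as the exposure, and for dilator use among EBRT+BT women;
- all of these results are reported as exploratory, because the sample size assumes no interaction.

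If a two-arm model was always intended, the same sentence makes that clear. No new data are needed. The cost is power: about 29% for a 0.5 SD difference in effect with 64 per arm and an even split, so a null interaction should not be read as a uniform effect.

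### The per-protocol contrast filters only the intervention arm on compliance, and the adherence correlation uses an effect no woman reveals; neither estimates a causal effect, though the intention-to-treat result is untouched

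*Protocol article*

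**What the plan says.** In the protocol article, Statistical analysis, the group comparisons of primary and secondary outcomes over T1-T5 "will be evaluated using multilevel models and are based on an intention-to-treat approach". Two further analyses follow. "Per protocol analyses will also be carried out (as a secondary analysis"), and the contrast is described as "comparing women who meet minimal compliance levels with the intervention with the control group". The restriction applies to the intervention arm; none is stated for controls. Then: "We will use correlation analyses to examine the relationship between degree of intervention adherence and intervention effect".

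Other sections bear on who can comply:

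- **Intervention group:** sessions take place at 1, 3, 6 and 12 months after radiotherapy. Women treated with EBRT+BT are offered one more at 2 months, and an optional further contact is available between 6 and 12 months.
- **Power and sample size calculation:** 40% attrition is expected, described as "women who discontinue participation in the study due to somatic reasons such as cancer recurrence".
- **Data collection:** data gathered before withdrawal stay available for analysis.
- **Other study parameters:** nurses record the type, length and modules of each session.

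**The concern.** Randomisation makes the two full arms comparable. Removing non-compliers from one arm and nobody from the other undoes this: the women left differ from controls both in what they received and in whatever made them comply. A threshold defined in a separate analysis plan would not cure this, because the fault lies in the one-sided contrast, which the article itself fixes.

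The correlation has a different fault. A woman's own intervention effect is the difference between her outcome with and without the programme, and only one of the two is seen. In practice adherence can only be correlated with outcome or change within the intervention arm. That association mixes any effect with prognosis (women who stay well can attend later sessions), need (the programme is tailored and the extra contact is by preference) and radiotherapy type (EBRT+BT women have one more scheduled session).

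What is at stake is interpretation. A per-protocol estimate larger than the intention-to-treat one, beside a positive adherence correlation, looks like support for efficacy but could arise with no effect at all.

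**Working it through.** **1. The plan's own figures.** Inputs from Power and sample size calculation: 0.5 SD, 80% power, two-sided 0.05, 40% attrition. A two-sample t-test needs 63.8, so 64 per group; power at 64 is 0.801. Inflation: 64 / 0.6 = 106.7, so 107 per group, 214 in total, rounded up to 220. At full recruitment 220 × 0.6 = 132 women are evaluable, 66 per arm. The figures reproduce, and nothing in this point changes them.

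**2. Bias of the per-protocol contrast with no true effect.** Let a fraction c of the intervention arm comply, namely those highest on a latent compliance score that has correlation r with the untreated outcome. With z the (1 − c) normal quantile and φ the normal density, compliers differ from the full arm, and so from controls, by

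bias (in SD) = r × φ(z) / c.

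Neither c nor r is in the article; both are assumptions.

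- c = 0.7: z = −0.524, φ(z) = 0.348, φ(z)/c = 0.497
- c = 0.6: z = −0.253, φ(z) = 0.386, φ(z)/c = 0.644

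| r | bias, c = 0.7 | bias, c = 0.6 |
|---|---|---|
| −0.3 | −0.15 | −0.19 |
| 0 | 0 | 0 |
| 0.1 | 0.05 | 0.06 |
| 0.2 | 0.10 | 0.13 |
| 0.3 | 0.15 | 0.19 |
| 0.4 | 0.20 | 0.26 |

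Over r = 0.1 to 0.4 the bias is 0.05 to 0.26 SD, about 10% to 52% of the 0.5 SD target.

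**3. False-positive rate.** With 66 controls and 66c compliers, a nominal 5% two-sided test rejects in 6%, 8% and 12% of trials at c = 0.7, and in 6%, 10% and 16% at c = 0.6, for r = 0.1, 0.2 and 0.3.

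**4. A randomisation-based alternative.** The complier average causal effect is the intention-to-treat difference divided by the compliance rate. With no true effect it is centred on zero whatever r is, because nobody is removed from either arm. That is a direct consequence of its form, not evidence that it is free of assumptions.

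**5. Why the threshold should be single and low.** The estimate assumes that attendance below the threshold has no effect. Suppose each session adds 0.125 SD and 10/10/10/20/50% attend 0/1/2/3/4 sessions (assumed figures). The intention-to-treat effect is 0.125 × (0.1 + 0.2 + 0.6 + 2.0) = 0.3625 SD.

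| threshold (sessions) | share reaching it | estimate | true mean effect in them |
|---|---|---|---|
| 1 | 0.9 | 0.40 | 0.40 |
| 2 | 0.8 | 0.45 | 0.44 |
| 3 | 0.7 | 0.52 | 0.46 |
| 4 | 0.5 | 0.73 | 0.50 |

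Higher thresholds credit the effect of partial attendance to fewer women. The estimate then rises faster than the truth and imitates a dose-response.

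**The case against.** The strongest reply is that these analyses are supportive. The article labels the per-protocol analysis secondary and bases the group comparisons on intention-to-treat; nothing says either result would rescue an unclear main result. This stands, and it limits the weight of the point.

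A reader might infer that both analyses are bound to favour the intervention. The article does not support that. Women with more problems may take up more sessions, which would reverse the per-protocol bias and weaken or invert the correlation. Expected loss through illness, and sessions running to 12 months, make bias toward the intervention plausible but not certain.

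A reader might also infer that, by the protocol's own account, intervention women miss sessions because of recurrence while equally ill controls stay in. The sample-size section describes women leaving the study and applies the same loss to both arms, so ill controls leave too. What is one-sided is narrower: the removal of women who stay but attend too little, and the early scores of controls who later leave, which are kept while comparable intervention women may be dropped. The article gives no size for either.

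The meaning of minimal compliance, and any adjustment for its predictors, may be set out in an analysis plan that is not shown. Their absence is not held against the article.

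None of this makes the planned contrast interpretable. A bias of uncertain sign is still a bias.

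**Conclusion.** The point holds as one about two secondary analyses. As written, the per-protocol contrast is not a randomised comparison, and the correlation is a confounded within-arm association; neither estimates a causal effect of the programme. Under 60-70% compliers and a correlation of 0.1-0.4, both assumed, the per-protocol contrast is shifted toward the intervention by about 0.05-0.26 SD with no true effect. With no correlation there is no shift, and with a negative one it favours control. The model also takes a normally distributed outcome and does not represent attrition. Women lost from both arms have no later scores, which limits the bias at 12 months.

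A reader might go further and conclude that the trial's efficacy result is compromised. It is not: the intention-to-treat comparison does not depend on either analysis. The change is worth making because it is cheap and because the unclear-result case is where these analyses would be most tempting to lean on.

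**What to change.** - State that the intention-to-treat analysis is the only basis for the efficacy conclusion.
- Replace the per-protocol contrast with one complier average causal effect in all randomised women, with randomisation as instrument. Fix a single low compliance threshold before database lock, for example at least one session attended, so that attendance below it can have little effect. The session records already planned supply the data.
- Use the same missing-data handling as the intention-to-treat analysis, since the instrument does nothing about 40% attrition.
- Add a note on control contamination, which the Discussion acknowledges. If controls received part of the programme, dividing by intervention-arm attendance alone does not recover the effect against no programme.
- Drop the adherence correlation, or report it as descriptive and non-causal. Do not present estimates at several thresholds as a dose-response.

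**Cost:** some analysis-plan wording and a small amount of programming. The interval widens by about one over the compliance rate: 1/0.9 = 1.11 times at 90% attendance, 1/0.7 = 1.43 at 70%, 1/0.6 = 1.67 at 60%. The estimate also rests on the exclusion restriction, that allocation affects outcome only through attendance. The booklet and, where applicable, the dilator set go to both arms, which makes this more plausible at a one-session threshold, but it cannot be tested.
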